### Treatment plan

The location of treatment delivery is decided at the point of trial entry. Once a patient had been randomised to a treatment location, the Investigator will define the treatment plan for the duration of the study period. Treatment will commence within 28 days of randomisation. A written summary of the treatment plan and emergency contact details will be provided to the patient. In all cases, the Investigator will prescribe treatment according to standard local practice.

For hospital-treated patients, all routine investigations and clinic appointments will be arranged according to standard clinical practice. For community-treated patients, the clinician will establish, with the community chemotherapy nurses, the treatment and follow-up arrangements for the patient for the duration of the study. This includes scheduled treatment times, need for any additional investigations and clinic appointments up until the end of the study period.

The chemotherapy nurses in hospital or the community will liaise with the Investigator to ensure the treatment plan for the patient is adhered to. They will document any deviations from the initial treatment plan and reasons for deviation. They liaise directly with the Investigator (or a member of his/her team) regarding any issues related to the patient's treatment. During the study, patients are asked to use the emergency contact details provided should problems of any kind arise.

### Study patient groups

#### Hospital (control) arm

Patients receiving treatment in hospital have their treatment delivered by appropriately trained chemotherapy nurses as per standard policies and procedures in each hospital.

#### GP surgery arm

Patients allocated treatment at a GP surgery are given the choice of being treated in one of 3 local surgeries in the area: The Christmas Maltings and Clements Surgery, Haverhill, East Barnwell Health Centre, Cambridge, or the Swan Surgery, Bury St Edmunds. All GP surgeries have generous, free parking facilities and their locations provide convenience for patients attending CUH and WSH. Patients entering this study do not have to be registered with these GP surgeries. All patients receive visual and written information regarding the geography of the surgeries as part of the invitation to take part in the trial to assist with their choice of surgery. Following allocation to this arm of the trial, a more detailed information leaflet and map describing the treatment venue is provided.

#### Home arm

Delivery of treatment in the home is delegated to trained chemotherapy nurses employed by CUH and WSH

### Patient assessments

Blood tests, radiological investigations and clinician reviews are undertaken on patients in all arms of the study, as per standard practice defined for each disease site and treatment regimen being used. Patients receiving treatment in the community have blood taken in the community and sent to the hospital laboratory so that the result is available to the Investigator on the day that treatment is due.

Prior to each course of treatment, patients receiving treatment in hospital are seen by the Investigator or delegated team member as per standard clinical practice, before proceeding with treatment. Patients receiving treatment in the community are assessed by the community chemotherapy nurse, who liaises with the prescribing clinician before proceeding with each course of treatment. Patients on any arm of the study can be referred for non-routine clinical review on request by another health care professional or on request by the patient. The frequency and reasons for extra clinical reviews will be monitored as part of the study, as part of adverse event reporting.

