### Secondary Aims

1) Other patient benefits identified using the Hospital Anxiety and Depression score, EQ-5D (EuroQol) and a specifically designed patient satisfaction questionnaire.

2) Qualitative assessment of the experience of treatment delivered in the three different locations, using semi-structured interviews of patients, their carers (where appropriate), and other health care professionals (doctors, nurses and hospital managers either directly or indirectly associated with this study).

3) Impact on costs and cost-effectiveness of treatment delivered in the three different locations. It will evaluate whether community care is cost-effective by measuring the costs and benefits to the NHS and to patients.

4) Patient safety, determined by the number of adverse and serious adverse events.

5) Compliance with treatment delivered in the different locations.

6) Assessment of reasons why patients decline to take part in the study.

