### Safety procedures

#### Adverse events

For the purposes of this trial, an adverse event (AE) is defined as:

- any unscheduled contact (e.g. phone calls, face-face visits etc) made by the patient, or carer to the outpatient or community treatment nurse, Investigator or member of his/her team, GP, or other support staff in relation to their current course of treatment.

- any unscheduled contact (e.g. phone calls, face-face visits etc) made by the out-patient, or community treatment nurse to the Investigator or member of his/her team, GP, or other support staff relating to the management of the patient receiving treatment.

To ensure accurate collection of trial-specific AEs, trial patients and treatment delivery nurses are issued with a purpose-designed diary in which to record all occasions when unscheduled contact is made. Specific information regarding contact is also requested. All AEs which occur from randomisation until the final trial visit are recorded. Specific information to be recorded in the diary regarding AEs includes the date and time of occurrence, main reason for making contact, with whom contact is made and outcome.

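### The adverse event count depends partly on what care is already scheduled, and that differs by arm, so a raw total is not a clean between-arm safety comparison

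*Protocol article*

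**What the plan says.** Safety is a secondary aim: "Patient safety, determined by the number of adverse and serious adverse events" (Protocol article, Secondary Aims). The Patient safety section repeats this and states the hypothesis that patients treated in the community are not harmed by it.

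Under Adverse events, an AE is not a clinical finding. It is an unscheduled contact of one of two kinds: one started by the patient or carer, or one "made by the out-patient, or community treatment nurse to the Investigator or member of his/her team", or to the GP or other support staff. Patient assessments adds non-routine reviews: "The frequency and reasons for extra clinical reviews will be monitored as part of the study, as part of adverse event reporting".

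The same section sets the routine check before each course:

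- Hospital arm: "patients receiving treatment in hospital are seen by the Investigator or delegated team member as per standard clinical practice".
- Home and GP surgery arms: "Patients receiving treatment in the community are assessed by the community chemotherapy nurse, who liaises with the prescribing clinician before proceeding with each course".

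Under Serious adverse events, drug-related reporting is limited to severe or life-threatening toxicity. The serious adverse event (SAE) list also includes a switch from community to hospital treatment.

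**The concern.** A count of unscheduled contacts and extra reviews is measured against a baseline of scheduled care. If that baseline differs by arm, a uniformly worded rule can give different counts for the same underlying problems.

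The routine pre-course check is where the baselines differ. A clinical contact is built into it in hospital. In the community it is a nurse assessment with a planned link to the prescriber.

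At stake is how the safety result is read. The AE number is half of the stated safety measure, and below grade 3 it is the only AE measure described. A difference in totals could be taken as harm or benefit of the venue when part of it reflects how care is scheduled. Equal totals could likewise hide a difference.

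**Working it through.** **Step 1: follow one problem through each arm.** Suppose a problem found at the pre-course check needs a clinician to see the patient.

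- Hospital: the Investigator or delegate is already seeing the patient as routine care. The problem can be settled there, with no unscheduled contact and no extra review, so it adds 0 to the count.
- Community: the nurse finds it and raises it in the planned liaison. The liaison is scheduled and adds 0. If direct review is then needed, that is a non-routine review, which is monitored within AE reporting and adds 1.

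If the liaison alone settles the problem, both arms add 0. Contacts between visits follow the same rule in every arm and are not affected. The non-comparable part is therefore limited to problems that surface at the pre-course check and go beyond planned liaison.

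**Step 2: is there a stated figure to reproduce?** The protocol gives no AE rate. Its only figure used here is 130 randomised per arm (Sample size), which makes 2 × 130 = 260 community patients. That figure reproduces: 91 evaluable per arm for 10 points, SD 24, 80% power and 5% significance (taken as two-sided), and 91 / 0.70 = 130. It sizes the primary endpoint and says nothing about AEs.

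**Step 3: illustration on assumed inputs.** None of these is in the document:

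- k = pre-course checks in 12 weeks (1 to 12; 4 for 3-weekly treatment)
- p = share of checks with a problem needing clinician input (5% to 20%, equal in all arms)
- a_h = share of those absorbed without an AE by the hospital review
- a_c = share absorbed without an AE by the planned community liaison
- μ = 1 other AE per patient in every arm

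Difference per patient, community minus hospital = k × p × (a_h − a_c).

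Rate ratio = [μ + k p (1 − a_c)] / [μ + k p (1 − a_h)].

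With k = 4 and p = 10%, k p = 0.40:

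| a_h | a_c | Difference per patient | Over 260 patients | Rate ratio |
|---|---|---|---|---|
| 100% | 50% | +0.20 | +52 | 1.2 / 1.0 = 1.20 |
| 100% | 75% | +0.10 | +26 | 1.1 / 1.0 = 1.10 |
| 75% | 50% | +0.10 | +26 | 1.2 / 1.1 = 1.09 |
| 75% | 75% | 0 | 0 | 1.00 |
| 50% | 75% | −0.10 | −26 | 1.1 / 1.2 = 0.92 |

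Range over k and p at a_h = 75%, a_c = 50%:

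- k = 1, p = 5%: 0.05 × 0.25 = +0.0125 per patient, about 3 events, ratio 1.025 / 1.0125 = 1.01.
- k = 12, p = 20%: 2.4 × 0.25 = +0.60 per patient, 156 events, ratio 2.2 / 1.6 = 1.38.

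With the two shares swapped, the last case gives −0.60 and 1.6 / 2.2 = 0.73. The artefact vanishes only when a_h = a_c, and nothing in the protocol makes them equal. No false-positive rate is given, because the Statistical Analysis section describes no test of AE counts.

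**The case against.** The case on the other side is substantial and narrows the point.

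- **The liaison is planned.** It takes place before every community course, so it is not an unscheduled contact. This stands. Only problems that exceed it remain.
- **The pathways overlap.** Patient assessments provides clinician reviews per standard practice in all arms and opens non-routine review to every arm. Treatment plan has nurses in both settings liaise with the Investigator. The hospital arm has treatment nurses too ("Patients receiving treatment in hospital have their treatment delivered by appropriately trained chemotherapy nurses"), and their unscheduled contacts count in the same way. This shrinks the contrast but does not make the pre-course checks the same.
- **Some of the difference is the intervention.** If nurse-led assessment generates more unplanned clinician input, that is a real effect of venue. This is true for workload and cost, but it is not evidence of harm, which is what the hypothesis concerns.
- **The article is condensed.** Forms and tables may be settled elsewhere, so the lack of a flag or a split table is not itself a fault. The AE definition and the two pathways, however, are stated here, and the point rests on those.

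Two stronger readings are tempting. A reader might infer that the count is biased against community care. The documents do not support a direction: the absorbed shares are unknown, and the illustration includes zero and reversal.

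A reader might also infer that the diary cannot separate these contacts, or that hospital events go unrecorded because the diary is for patients and nurses ("trial patients and treatment delivery nurses are issued with a purpose-designed diary in which to record all occasions when unscheduled contact is made"). That is not supported either. The listed items are introduced as inclusions, not as a complete list. They cover date and time as well as "main reason for making contact, with whom contact is made and outcome", and dates can be set against treatment dates. Patients in every arm hold a diary, and the monitoring of extra reviews is not confined to diary holders.

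**Conclusion.** The point holds in a limited form. As defined, the AE count mixes patient problems with the arm's schedule of routine care, so a raw total does not cleanly compare arms for the no-harm hypothesis. It rests on one reading of the text: that a problem needing direct clinician review at the pre-course check can be dealt with inside the routine hospital visit but becomes an extra review in the community.

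Size and net direction are not fixed by the document. The ratios above show only that the effect could be negligible or material in either direction.

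This is minor. It concerns a secondary endpoint. The primary analysis is untouched, and so are the SAE criteria that do not involve venue: death, life-threatening events, hospitalisation and grade 3 or 4 toxicity.

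**What to change.** Do not use one AE total as the between-arm safety measure. Instead:

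1. Report AE counts by arm in three rows: patient- or carer-initiated contacts, nurse-initiated contacts and extra clinical reviews.
2. Show those arising at a pre-course check separately, using a one-item flag in all arms or by matching the recorded contact date to treatment dates.
3. State that planned pre-course liaison is not counted.
4. Base the between-arm safety conclusion mainly on the clinically defined SAEs that apply in all arms: death, life-threatening events, hospitalisation and grade 3 or 4 toxicity. Leave out the switch to hospital treatment, which cannot occur in the hospital arm, and report it on its own.

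The cost is more rows in the safety table, one extra diary item if the flag is chosen, and no single headline AE count. No data are discarded, and the contact counts remain usable for workload and cost. Asking the hospital reviewer to record problems settled within the routine visit would sharpen the comparison further, but it is optional.

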### Concomitant medication

Patients may receive all concomitant therapy deemed to provide adequate supportive care. Since this trial is not directly interested in treatment *per se*, concomitant medications will not be systematically recorded. However, information about ongoing treatment at the time of study entry and changes in treatment during the course of the study will be recorded by the patient in the Client Service Receipt Inventory (CSRI). In addition, records of drugs prescribed by the hospital and the patient's own GP will be obtained.

### Recording and collection of data

Upon randomisation of an individual patient, a pack containing specifically designed data collection forms, questionnaires and diaries is provided to the Investigator. The forms allow collection of essential information required for the study at each predefined trial data collection point. The study has four mandatory and 1 optional data collection point. Mandatory data collection points are baseline (at the start of study treatment), then approximately 4 weeks, 8 weeks and 12 weeks after commencing treatment. For patients continuing treatment beyond 12 weeks, there is an optional data collection point at 24 weeks or on stopping treatment, whichever occurs sooner. The baseline, 12 week and 24 week data collection visits take place at hospital. On these occasions, study forms will be completed by the Investigator or a member of his/her team, which may include a specialist or research nurse/practitioner. Patient questionnaires and diaries are given to the patient and/or collected from the patient as appropriate at these visits.

In order to allow for different treatment schedules, the second and third data collection points may be flexible to within 1 week either side of the planned 4 and 8 week time points. For patients having treatment in hospital, on these occasions, forms are completed by the Investigator or a member of his/her team, which may include a specialist or research nurse/practitioner. Patient questionnaires are given to and collected from the patient as appropriate at these visits. For patients having treatment in the community, these study forms are completed by the community chemotherapy nurse. Patient questionnaires are given to and collected from the patient as appropriate at these visits.

Following each planned data collection point, study forms and questionnaires are returned to the Outreach Trial Coordinator, who is responsible for creating and completing the unique patient Case Report Forms (CRF).

Patients randomised to receive treatment in either community setting may be transferred at any time to continue treatment in hospital, and the date and reason for transfer will be documented. Transfer of care to the hospital constitutes a serious adverse event (SAE) and withdrawal from the trial. Patients randomised to receive treatment in hospital may not be transferred to either location in the community, since this is not standard clinical practice locally.

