### Patient registration and randomisation

Eligible patients are registered with and randomised by the Outreach Trial Co-ordinator, at the Cambridge Cancer Trials Centre (CCTC), CUH. Eligible patients are allocated a unique trial number and the treatment location defined. Registration and randomisation is undertaken by fax or email and the randomisation outcome information provided to the Investigator by return, within 24 hours. The Investigator is responsible for organising the patient's treatment and follow-up.

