### Study procedures

The study procedures are summarised in Table 1.

**Table 1 T1:** Study measures and timing

	Data point 1: Baseline, prior to commencing treatment	Data point 2: 4** weeks into treatment	Data point 3: 8** weeks into treatment	Data point 4: 12 weeks into treatment	Data point 5: 24*** weeks into treatment
Clinic Review*	x			x	X

PS	x	x	x	x	X

Weight	x	x	x	x	

Blood tests*	x				

Radiology*	x				

EORTC QLQC30.	x	x	x	x	X

HAD, EQ-5D and Patient Satisfaction Questionnaire	x	x	x	x	X

CSRI Completion	x			x	

Patient Diary for AE Recording	x	x	x	x	X

Semi-Structured Interview	x(1 in 10 patients)			x	

*Clinic review, blood tests and radiological investigations will be carried out according to standard clinical practice at baseline and during the study period.

** +/- 1 Week

*** For patients whose treatment continues beyond 12 weeks, patients will complete a further set of trial assessments when their treatment stops or at 24 weeks, whichever is sooner. This data point is optional.

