### Outcome measures

#### Study end points

##### 1) Primary end point: Patient perceived benefit

Patient perceived benefit is quantitatively measured by determining overall quality of life using the EORTC QLQC30 instrument. The mean quality of life emotional function score will be compared between study populations, since this domain might be considered to best reflect the levels of anxiety and satisfaction felt by patients taking part in this study.

The QLQC30 questionnaire will be administered prior to randomisation, at 4 weeks, 8 weeks and 12 weeks. Where patients continued to receive the same treatment beyond 12 weeks, they are asked to complete a similar questionnaire once more when their treatment stopped, or at 24 weeks, whichever is sooner. Where a carer is identified, the carer is also asked to complete EORTC QLQC30 questionnaire at each time point.

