##### 2) Secondary end points

###### i) *Additional patient perceived benefits*

Additional comparisons of global quality of life, anxiety and overall satisfaction with treatment received are made by asking patients to complete three additional questionnaires, as follows:

- The EQ-5D (EuroQol) instrument

- The Hospital Anxiety and Depression (HAD) questionnaire

- A specifically designed patient satisfaction questionnaire

Each questionnaire is completed prior to randomisation, at 4 weeks, 8 weeks and 12 weeks. Where patients continue to receive the same treatment beyond 12 weeks, they are asked to complete a similar set of questionnaires when their treatment stopped or at 24 weeks, whichever is sooner. Where a carer is identified, the carer was also asked to complete the three questionnaires at each time point.

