### Statistical Analysis

The primary analysis time-point is 12 weeks. The primary contrast is between home and GP surgery arms combined, versus hospital arm. Binary outcomes will be analysed using logistic regression. Continuous outcomes will be analysed using linear regression adjusting for randomisation stratifiers and the pre-randomisation baseline of the outcome in order to improve precision of the estimated intervention effects. Participants with valid data at follow-up but with missing data at baseline will be retained in the analysis by using the missing indicator method [20]. For measures repeated over time, linear mixed models will be used to analyse data from all time-points together, to assess for any patterns between study arms. The level of missing data will be compared by study arm. A logistic regression model will be used to examine whether baseline factors or intermediate study measures predict dropout by 12 weeks. With sufficient 12-week data, the impact of missing data on the main outcomes will be assessed using best and worst case sensitivity analyses, using multiple imputation [21], or otherwise using the linear mixed effects model with the available 4-week and 8-week data to model the 12-week effect from the trend in the outcome over time in each arm. Further analyses will include comparisons between pairs of arms, analyses at time-points and subgroup analyses, with subgroups defined by treatment intent and hospital.

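### The protocol gives two incompatible times for the baseline questionnaires, and under one of them the baseline covariate in the primary analysis may be recorded after patients know their treatment venue

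*Protocol article*

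**What the plan says.** Three sections of the protocol article place the baseline before randomisation:

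- Primary end point: "The QLQC30 questionnaire will be administered prior to randomisation, at 4 weeks, 8 weeks and 12 weeks".
- Additional patient perceived benefits, covering HAD, EQ-5D and the satisfaction questionnaire: "Each questionnaire is completed prior to randomisation, at 4 weeks, 8 weeks and 12 weeks".
- Statistical Analysis, where continuous outcomes are modelled by linear regression "adjusting for randomisation stratifiers and the pre-randomisation baseline of the outcome".

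The section Recording and collection of data gives another timing. It states "Upon randomisation of an individual patient, a pack containing specifically designed data collection forms, questionnaires and diaries is provided to the Investigator", and describes the forms as serving every scheduled collection point. It then defines the first of these: "Mandatory data collection points are baseline (at the start of study treatment". It also has questionnaires handed out or collected at the baseline hospital visit.

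Two other sections fix the interval. Under Patient registration and randomisation, the allocation is returned quickly: "the randomisation outcome information provided to the Investigator by return, within 24 hours". Under Treatment plan: "Treatment will commence within 28 days of randomisation".

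Table 1 (Study procedures) heads its first column "Data point 1: Baseline, prior to commencing treatment". That fits either timing.

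**The concern.** The venue cannot be concealed from the patient. After randomisation the patient receives a written summary of the treatment plan, and a patient in the GP surgery arm chooses a surgery and receives a leaflet and map. The primary outcome is self-reported emotional function, chosen because it is thought to reflect anxiety and satisfaction. It could plausibly move when a patient learns where treatment will be given.

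A covariate measured before randomisation cannot be affected by allocation, so adjusting for it improves precision without bias. A covariate measured after allocation is known may already carry part of the effect, or a reaction against it, and adjustment then moves the estimate.

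The missing indicator method is exposed as well. Allocation cannot cause a pre-randomisation form to be missing. It can cause a later form to be missing, so arm-dependent baseline missingness becomes possible.

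**Working it through.** **Order of events under each timing**

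| Step | Outcome and analysis sections | Recording and collection of data |
|---|---|---|
| 1 | Baseline questionnaires completed | Randomisation; pack sent to the investigator |
| 2 | Randomisation | Allocation returned within 24 hours |
| 3 | Allocation returned within 24 hours | Treatment starts within 28 days; baseline at that start |
| 4 | Treatment starts within 28 days | |

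One form cannot be completed both before randomisation and at a treatment start that follows randomisation. No section reconciles the two.

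**The plan's own figures (Sample size section)**

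Inputs: difference 10, SD 24, 5% significance (taken as two-sided), 80% power, 30% missing outcomes.

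- n per arm = 2 × (1.960 + 0.842)² × 24² / 10² = 90.4, so 91. Then 91 / 0.70 = 130 randomised per arm, as stated.
- Pairwise power with 91 per arm = 0.803, matching the stated 80%.
- Combined community arms against hospital, 182 against 91: SE = 24 × √(1/91 + 1/182) = 3.08. Power = Φ(10/3.08 − 1.96) = 0.90, as stated.

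These figures reproduce and do not depend on when the baseline is taken.

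**Bias if the baseline follows allocation**

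Let b be the within-arm slope of the 12-week score on baseline. Let s be the between-arm difference in mean baseline caused by knowing the allocation (community minus hospital). Then

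expected adjusted effect = true effect − b × s.

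Neither b nor s is in the documents. Assume b = 0.5 to 0.6 and s = 3 to 5 points in either direction:

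- smallest bias: 0.5 × 3 = 1.5 points
- largest bias: 0.6 × 5 = 3.0 points

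With a true difference of 10, a shift in the direction of the effect gives an expected estimate of 8.5 down to 7.0. A shift against it gives 11.5 up to 13.0. With s = 0 the estimate stays at 10.

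**Power with an attenuating shift**

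An adjusted estimate needs an adjusted standard error. Taking equal SDs at baseline and 12 weeks, so that the slope equals the correlation, the residual SD is 24 × √(1 − b²).

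- b = 0.5: residual SD 20.8, SE = 3.08 × 0.866 = 2.67
- b = 0.6: residual SD 19.2, SE = 3.08 × 0.80 = 2.46 (from the unrounded SE)

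Power = Φ((10 − b × s)/SE − 1.96):

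| b | s = 0 | s = 3 | s = 5 |
|---|---|---|---|
| 0.5 | 0.96 | 0.89 | 0.80 |
| 0.6 | 0.98 | 0.91 | 0.81 |

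So power falls from 96-98% to about 80-91%.

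**The case against.** The best defence is that the timing is fixed where it matters. The sections naming the primary instrument, the secondary questionnaires and the covariate all say pre-randomisation, and Table 1 is compatible with them. The only outlier is a paragraph on form logistics. It does not say that the pack is the first or only source of the baseline QLQ-C30.

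Much of this stands. A reader might infer that the trial plans to adjust for a post-allocation covariate, or that its baseline is in fact contaminated. The article supports neither: it does not show which timing sites used, or that any shift occurred. What the defence does not remove is the conflict. The paragraph on logistics is the one that tells sites when to act. It defines baseline as treatment start, says the forms in the pack serve every collection point, and describes no earlier supply. Nor is this detail that a condensed article leaves to another document, because the article states both timings.

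A reader might also set the bias against the unadjusted SE of 3.08 and conclude that power drops from 90% to 62-79%. That does not hold. It combines the bias of an adjusted estimate with the standard error of an unadjusted one. If the slope is 0.5 to 0.6 the residual SD shrinks, and without adjustment this bias does not arise.

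Finally, it is tempting to treat attenuation as the expected direction and the missing indicator method as certain to fail. The shift could equally oppose the effect, for example through worry about leaving hospital, and inflate the estimate. Arm-dependent missingness is possible, not inevitable.

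**Conclusion.** The protocol contradicts itself on when the baseline is taken, and the primary adjusted analysis depends on which version is followed. That much rests on the text alone.

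The statistical consequence is conditional. It needs sites to follow the data collection section, patients to know their venue at baseline, and that knowledge to shift scores differently between arms. If all three hold, the bias is 1.5 to 3.0 points either way under the assumed slope and shift, or 15-30% of the 10-point target. Power stays at about 80% or above even when the shift attenuates. Zero shift means zero bias. The 130 per arm and the stated 80% and 90% power stand.

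It deserves correction because it affects the primary covariate, and a missing pre-randomisation form cannot be recovered once the patient has been randomised.

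**What to change.** Amend Recording and collection of data, and the first column of Table 1, to agree with the outcome and analysis sections. Suggested wording: *Baseline QLQ-C30, HAD, EQ-5D and patient satisfaction questionnaires are issued at consent and completed before the randomisation request is made. Only follow-up questionnaires are issued on randomisation.*

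In Statistical Analysis, add that only baseline forms dated before randomisation serve as the covariate, and that later-dated forms count as missing baseline under the missing indicator method already planned. Missingness defined in this way cannot be caused by allocation.

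The cost is small. The questionnaires are unchanged, and the patient is already seen in clinic before study entry, so no visit is added. The baseline pack goes out slightly earlier, and some baselines will be reclassified as missing, with a little loss of precision.
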